http://www.R-project.org/) on an intention to treat basis, and per protocol where possible. Results will be presented in terms of absolute and relative values with 95% confidence intervals where appropriate. Results will be considered statistically significant if the p-value ≤0.05.

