17^. A multimodal enhanced recovery programme (ERP), including IV TXA on induction of anaesthesia, was introduced in May 2008. In keeping with other similar policy changes in this unit, a 6-month implementation period for the ERP is considered appropriate. To account for this, data from 1
^st^ January 2008 to 31
^st^ October 2008 will be excluded from this analysis. In addition, patient warming has been introduced locally
^23^ but a Cochrane review shows this does not affect surgical transfusion rates, so will not be considered any further
^24^. Intra-operative cell salvage has never been routinely used locally for the procedures being studied. To the best of our knowledge, no other relevant co-interventions have been introduced during the study period. Any unaccounted for, gradual changes in practice, would be detected in the pre-intervention slope of the TXA analysis and in the control group for the anaemia analysis.

Other considerations include changes in data coding, validity and reliability over time. The data for this study is considered reliable as it comes from a number of NHS Trust electronic databases detailed earlier in this paper. There have been no material changes to data collection methods or outcome reporting over the study period.

Changes in the population over time can also affect ITS reliability. There have been no known substantial changes in the population served by NHCT over the study period; however, to explore this within the data, tables of patient demographics (i.e. age, sex) for each of the pre- and post-intervention periods will be produced and examined for differences. Should substantial differences be identified, these characteristics will be incorporated into the final model as covariates, where possible.

This study includes a continually enrolled population, so is not subject to population attrition over time. Although no changes to diagnostic criteria for ischaemic heart disease (IHD) are known to have occurred during the study period, this comorbidity is specifically mentioned in the NHCT transfusion policy and lowers the threshold for considering transfusion. For completeness, rates of IHD will be plotted against time and visually inspected for any patterns, particularly around the time of the interventions. If required IHD will be included in the ITS modelling.

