***Developing the model.*** Data will be inspected for outlier data points and, where identified, explanations will be sought and exclusion considered. First order lagged residuals will be included in the ITS models to account for autocorrelation
^20,
25^. The use of 6-month implementation periods in this study could be the same time between the lowest and highest points in an annual cycle, should seasonality affect outcomes. Although this is not expected in this instance, a sensitivity analysis including a lag of 12 time points (assuming seasonality) will be undertaken to test the robustness of the two primary analyses.

***Sensitivity analysis.*** An optimal model will be developed and described for these ITS analyses. The impact of decisions taken during this process such as inclusion/exclusion of outlying data points and autocorrelation adjustments will be tested in sensitivity analyses. Further analyses of data stratified by surgery type (THR or TKR) and/or by patient gender, will be conducted if data permits, as these may impact on outcomes.

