^28^. If differences are seen, and it is possible the more anaemic patients (lower Hb) have more comorbidities and/or are older, then variables which are identified as being different between the two groups will be included as covariates in the final model. Similar to ITS, RDD is sensitive to co-interventions introduced around the threshold Hb value. There are no known co-interventions introduced locally for this patient cohort around the threshold Hb values.

***Developing the model.*** In graphical representations of the data, Hb will be divided into bins. Outcome data for this study is in the form of discrete variables (yes/no: transfused / readmitted / critical care admission; and number of inpatient days). As such, outcome data will be converted to a probability (i.e. risk of transfusion) or average (i.e. mean number of days) for each bin. To decide optimal bin size, plots of Hb and primary outcome (transfusion rate) will be generated for a range of bin sizes (i.e. 1, 2 or 5 g/L). Visual inspection of these plots will be used to rule out bin sizes that are clearly too wide or too narrow. For the remaining bin sizes, F-tests using
*k*2 dummies and interactions will be performed to identify bin sizes that do not over smooth the data. From the remaining choices the widest bin size that is not rejected by either F-test will be chosen
^32^. The same bin size as chosen for the primary outcome will be used for plotting other outcomes to facilitate comparison. 95% confidence intervals will be plotted alongside the probabilities or averages where applicable.

Separate scatter plots of primary and secondary outcomes against Hb will be created. These will be inspected visually for a jump at the threshold value, indicative of a treatment effect. Data will be inspected for outlying data points and consideration given to exclusion. Sensitivity analysis with and without outlying data points will be performed.

As the sample size for this analysis is relatively small a parametric estimation of treatment effect will be used for the primary analysis using logistic regression
^32^. Length of stay will be considered as a continuous outcome. The F-test will be used to determine the optimal functional form of the parametric regression model. Starting with a simple linear model, a higher order term will be added to the model until the F-test is no longer statistically significant
^32^.

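### ITS case-mix adjustment is triggered by comparing period averages, which flags steady drift the trend term already removes and misses change that bends or resets around the intervention

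*SAP article*

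**What the plan says.** All of this is in the SAP article, section Interrupted Time Series.

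- **Addressing threats to validity, population change.** The check is one table per period: "tables of patient demographics (i.e. age, sex) for each of the pre- and post-intervention periods will be produced and examined for differences". The consequence is conditional: "Should substantial differences be identified, these characteristics will be incorporated into the final model as covariates, where possible". No threshold is given for a substantial difference.
- **Same subsection, IHD.** This variable has its own check and its own route into the model: "rates of IHD will be plotted against time and visually inspected for any patterns, particularly around the time of the interventions", and then "If required IHD will be included in the ITS modelling".
- **Sensitivity analysis.** Surgery type and gender also get a conditional stratified analysis: "Further analyses of data stratified by surgery type (THR or TKR) and/or by patient gender, will be conducted if data permits".
- **Addressing threats to validity, gradual change in practice.** The article states that unaccounted gradual changes "would be detected in the pre-intervention slope of the TXA analysis and in the control group for the anaemia analysis".
- **Table 3 and the text on the primary analysis.** The primary anaemia ITS includes all hip and knee patients without splitting them. The non-anaemic comparison series appears only in the secondary analyses. The TXA analysis has no control group at all.

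**The concern.** A segmented regression projects the pre-intervention line forward and asks whether the post-intervention series departs from it in level or slope. Case mix confounds that contrast when its path over time departs from a straight line at or around the intervention. Whether its average differs between the two periods is a different question, and the average is what the table shows.

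The rule can therefore err in both directions. It can call for adjustment that the trend term makes unnecessary, and it can stay silent where adjustment is needed. Defining substantial more precisely would not cure this, because the quantity being compared is the wrong one.

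The backstop is thinner than the text suggests. The article looks to the control group to reveal gradual change in the anaemia analysis, but the primary anaemia ITS has none. In the TXA analysis the pre-intervention slope deals with change that continues steadily, but not with change that stops or turns near the policy date. At stake is whether part of a reported level or slope change in either primary ITS could be case mix.

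**Working it through.** The article gives no case-mix, power or effect figure, so there is nothing to reproduce. The check asks how the rule behaves under different patterns of drift when the intervention has no effect.

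**Inputs from the article**
- Anaemia primary ITS: 12 months before, 6 excluded, 12 after. TXA: 33 before (November 2008 to July 2011), 6 excluded, 12 after.
- About 100 procedures a month.
- Significance rule: "Results will be considered statistically significant if the p-value ≤0.05" (taken as two-sided).

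**Assumptions, not in the article**
- Worked example: transfusion rate 5%; a risk factor with mean share 30% that rises by 6 or 10 points over the pre-period and is flat at 30% afterwards; risk difference 3 or 5 points.
- Simulation: risk factor with mean share 50%; drift of 10 to 30 points; transfusion risk without/with the factor of 4%/8% or 5%/15%.

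**Step 1: modest drift, by hand.** The table shows 30% against 30%, so nothing is triggered.

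False level change = −(drift ÷ (pre-months − 1)) × (distance from the pre-period midpoint to the first post month) × risk difference.

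- Anaemia (midpoint 6.5, first post month 19, distance 12.5): 6/11 × 12.5 × 0.03 = 0.20 points; 10/11 × 12.5 × 0.05 = 0.57 points. Both are falls.
- False slope: 6/11 × 0.03 = 0.016 and 10/11 × 0.05 = 0.045 points a month, both downward.
- TXA (midpoint 17, first post month 40, distance 23): 6/32 × 23 × 0.03 = 0.13 points; 10/32 × 23 × 0.05 = 0.36 points.

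**Step 2: set this against the standard error.** The SD of a monthly rate is √(0.05 × 0.95 / 100) = 2.18 points.

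- Anaemia level: 2.18 × √(1/12 + 12.5²/143 + 1/12 + 5.5²/143) = 2.18 × 1.213 = 2.64 points. The bias is 0.20/2.64 = 0.08 to 0.57/2.64 = 0.21 SE.
- Anaemia slope: 2.18 × √(2/143) = 0.26 points a month. The bias is 0.06 to 0.18 SE.
- TXA level: 2.18 × √(1/33 + 23²/2992 + 1/12 + 5.5²/143) = 1.54 points. The bias is 0.08 to 0.23 SE.
- False-positive rate per test: at most about 5.5% (anaemia) and 5.6% (TXA), against a nominal 5%.

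**Step 3: larger drift, by simulation.** Least squares on monthly proportions, without the lagged-residual term, 4,000 runs per scenario. The table check was approximated by a two-proportion z test at 0.05, since the article sets no threshold.

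| Case-mix pattern | Flagged by table | False effect | Rejection of the affected test |
|---|---|---|---|
| Steady linear drift through both periods | 86–100% | exactly 0 | about 5% |
| Step at the intervention | about 100% | level biased | not needed, since the table catches it |
| Anaemia: up then down, 20–30 points, 4%/8% | about 5% | slope −0.15 to −0.22 points/month | 8–12% |
| Anaemia: up then down, 20–30 points, 5%/15% | about 5% | slope −0.36 to −0.55 points/month | 16–31% |
| Anaemia: up, reset, up, 20–30 points, 4%/8% | about 5% | level −1.3 to −2.0 points | 8–10% |
| Anaemia: up, reset, up, 20–30 points, 5%/15% | about 5% | level −3.3 to −4.9 points | 14–25% |
| TXA: up, reset, up, 20–30 points, 4%/8% | about 5% | level −1.0 to −1.5 points | 8–13% |
| TXA: up, reset, up, 20–30 points, 5%/15% | about 5% | level −2.4 to −3.7 points | 21–39% |

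With equal period averages the table fires only at its chance rate. At 10 points of drift, rejection is at most about 7% (anaemia) or 9% (TXA).

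**Step 4: does always adjusting help?** In the anaemia design (3,000 runs), monthly rates were adjusted to a fixed share using the within-month risk difference. In the 5%/15% reset scenarios the false level fell from −3.3 and −4.8 points to within 0.1 of zero, and rejection fell from 14–25% to 5–6%. Entering the monthly share itself as a covariate also removed the bias, but raised the SD of the level estimate, for example from 3.6 to 7.8 points, because a drifting share is nearly collinear with the segment terms.

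**The case against.** The strongest reply is that the failing pattern is special. Drift must bend, stop or reset near the policy date while leaving the period averages equal. The article reports no known substantial change in the population served, and nothing in it suggests such a pattern. The most direct threat to the level estimate, a step in case mix at the intervention, is exactly what the table catches. At modest drift the bias is a small fraction of a standard error. All of this stands, and it limits the size of the point. It does not make the period table the right check for this model.

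Three stronger readings are tempting but not supported.

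- **That any drifting case mix creates a false effect.** It does not: steady linear drift gives exactly zero false level and slope change.
- **That the plan checks no case-mix variable over time, or ignores surgery type.** IHD is plotted against time and may enter the model. Surgery type and gender have conditional stratified analyses. The article names age and sex with a loose abbreviation that it uses elsewhere for examples, so its wording does not clearly exclude surgery type from the tables.
- **That the regression discontinuity analysis has the same defect.** Its final model does select covariates by observed difference ("variables which are identified as being different between the two groups will be included as covariates in the final model"). However, covariate-adjusted sensitivity analyses are planned there however comparable the groups prove, so an adjusted result will exist in any case.

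The secondary anaemia analyses do have a non-anaemic comparison series, which gives some protection, but not to the primary analysis.

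**Conclusion.** The point holds in limited form. For age, sex and other tabulated characteristics, entry into the ITS model depends on a comparison that does not match what a segmented regression estimates. It flags steady drift that does no harm and misses change that is non-linear or turns around the intervention with equal averages. Neither primary ITS has a control series to fall back on, although the article invokes one for the anaemia analysis.

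The expected size is small: about 0.1 to 0.2 SE on the level change for an assumed 6 to 10 point drift. False-positive rates of 14–25% (anaemia) or 21–39% (TXA) on the level test require an assumed 20 to 30 point drift that resets at the intervention, in a factor that triples transfusion risk (5% to 15%). All drift and risk values are assumptions, and the calculations omit the planned autocorrelation term. A reader should not infer that the primary results will be biased. The case for change is that the stated rule is mismatched and the remedy is cheap.

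**What to change.** 1. Examine age, sex and joint (hip or knee) month by month, in the way already planned for IHD, in place of relying on one table per period.
2. For both primary ITS analyses, pre-specify a version adjusted for age, sex, joint and IHD whatever the tables show, and report it beside the unadjusted model.
3. Obtain the adjustment from procedure-level segmented logistic regression, or from monthly rates standardised to a fixed case mix. Do not enter monthly aggregate shares as covariates, because of the loss of precision shown above.
4. Correct the statement that a control group will reveal gradual change in the anaemia analysis, so that it refers only to the secondary analyses that have one.

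The article describes a procedure-level dataset with demographics, comorbidities and operative details, so no new data collection should be needed. The cost is slightly more analysis work and a second reported model. The procedure-level option also departs from the monthly aggregation now described, so it needs its own short model specification; standardised rates keep the monthly format.

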### Interrupted Time Series

ITS using segmented regression has several strengths over the pre-post study design. It controls for secular trends over time, provides powerful, easy to understand visual outputs, and may improve generalisability to the wider population
^7,
8,
19^. For this study, data are available to evaluate both policies described above in an ITS analysis.

The two interventions in this study were introduced at specific, well defined time points, allowing for clear separation of pre- and post-intervention periods.
Figure 1 provides a timeline for the interventions in questions and
Table 3 provides details of the planned analyses and time periods included in each. As shown in
Figure 1, the same 12-month time period is used for both ITS analyses meaning they are not independent. However, there is insufficient time or data points to prevent this overlap, and this will be discussed as a potential limitation of the study.

**Table 3. T3:** Planned ITS analyses.

Policy change	Dates	Analyses
Change in TXA dose policy	Pre-intervention 01/11/2008 – 31/07/2011 Excluded implementation (lag) period 01/08/2011 – 31/01/2012 Post-intervention * 01/02/2012 – 31/01/2013	PRIMARY – Population-level effects of TXA policy for all patients undergoing THR or TKR
Introduction of preoperative anaemia screening programme	Pre-intervention * 01/02/2012 – 31/01/2013 Excluded implementation (lag) period 01/02/2013 – 31/07/2013 Post-intervention 01/08/2013 – 31/07/2014 (sensitivity analysis 01/08/2013 – 28/02/2019)	PRIMARY – Population-level effects of anaemia screening programme for ***all patients*** undergoing THR or TKR (with equal number of data points pre- and post-intervention)
		SECONDARY - Effect on anaemic subpopulation ***eligible for any*** ***treatment*** as per anaemia pathway (Hb <120g/L, female or 130g/L, male) **, modelled against non-anaemic cohort
		SECONDARY - Effect on anaemic subpopulation ***eligible for iron*** treatment only (Hb 105–119g/L female, 115–129g/L male & ferritin 12- 100), modelled against non-anaemic cohort (excluding those with Hb <105 or <115 and those referred to GP/haematologist).
		SECONDARY - Effect on anaemic subpopulation ***given iron*** treatment only (as above but only those given iron), modelled against non-anaemic cohort (same exclusion as above) – per protocol analysis

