* Post-intervention period for TXA policy is the same as the pre-intervention period for anaemia screening programme analysis. **includes GP referral, haematology referral or any form of iron

An early step in ITS analysis is to generate summary statistics for each time period and undertake simple pre-post comparisons
^20^. This will be performed in this study and later compared to the results from ITS and RDD analyses.

***Data description.*** ITS is said to work best with short-term outcomes that change quickly after implementation of an intervention or after a clearly defined lag period
^8^. This study is examining short-term outcomes; however, some delays to observed changes in outcomes after policy implementation are expected. The orthopaedic department has previously reported that a 6-month lag period was required to fully adopt the increased TXA dose policy
^16^. This same lag will therefore be incorporated into this ITS analysis. Regarding the introduction of the preoperative anaemia screening programme, staff running the anaemia service report that this started promptly on 01/02/2013, after detailed planning, and uptake was rapid. However, a lag to observed changes in outcomes will be inevitable due to surgical waiting list times. Comparing screening and surgery dates for the first 10 anaemic and 10 non-anaemic patients from the cohort shows all but one had their surgery within 6 months of screening. Therefore, a 6-month implementation (lag) period is also considered appropriate following introduction of the anaemia screening service (
Figure 1). Lag periods will be accounted for by excluding this data from the primary analysis
^21^. As individual procedure-level data are available, including data indicating whether or not anaemia screening was received, an alternative approach to handling the lag period for the analysis of the anaemia screening programme, could be to model the intervention as a continuous implementation variable ranging from 0 to 1, instead of as a binary (0/1) variable. This would allow the effect of the intervention to be modelled as a weighted average during the 6-month implementation period, which could be a more efficient use of the data available. A sensitivity analysis of this alternative method for handling the 6-month implementation period will be included in this study.

ITS requires sequential measures of the outcome, at regular intervals, before and after the intervention time points
^20,

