21^. In keeping with many ITS studies, individual-level outcome data will be converted to, and presented as, proportions or means at monthly intervals and a segmented-regression analysis performed
^21^. ITS plots will be generated and visually inspected to determine if linear or non-linear regression modelling is appropriate. A minimum of 8 data points pre- and post-intervention are desirable
^20,
21^. It is expected the shortest time frame being analysed in this study will include 12 months/data points, thus surpassing this requirement. The power of an ITS analysis is increased if there are an equal number of data points pre- and post-intervention
^22^. In the case of preoperative anaemia screening there are expected to be 12 data points in the pre-intervention period but 60 in the post-intervention period. As such, to increase power of this analysis this period will be cut to include only 12 time points, after the 6 month lag period, for the primary analysis of the anaemia screening policy. Sensitivity analysis including all post-implementation data points will be conducted.

***Addressing threats to validity.*** Time varying confounders are the main threat to the validity of ITS studies
^21^. These are specific to each ITS study and are carefully considered later in this SAP. However, the most robust way to account for time varying confounders, even those that are unknown, is to model against a control group. This could either be a different population not exposed to the intervention or, if individual-level data are available, by splitting the data into two groups, one group targeted by an intervention and another that is not. In this study, data for a different group of patients is not available for either intervention. The TXA policy is targeted at all THR or TKR patients so this data cannot be split. However, the anaemia screening policy targets a specific subgroup of anaemic patients with treatments so the population can be split into two groups to increase the robustness of this analysis. As such the two interventions will be modelled separately: 1) the TXA intervention without a control group, and 2) the anaemia screening intervention with a control group.

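### If lagged residuals are added as a covariate, the two primary ITS tests stay uncorrected for positive autocorrelation; the plan should name an AR(1) error model

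*SAP article*

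**What the plan says.** The ITS analyses use monthly aggregates: "individual-level outcome data will be converted to, and presented as, proportions or means at monthly intervals and a segmented-regression analysis performed" (Interrupted Time Series, Data description). The only adjustment fixed for serial correlation is one sentence under Developing the model: "First order lagged residuals will be included in the ITS models to account for autocorrelation". It carries two citations. No estimator is given, no check of residual autocorrelation is planned, and no AR error model, generalised least squares or robust standard error is named.

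Inference is by p-value and interval. The end of Data source states: "Results will be considered statistically significant if the p-value ≤0.05" and "Results will be presented in terms of absolute and relative values with 95% confidence intervals where appropriate".

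Table 3 and the surrounding text fix the series:
- TXA: "Pre-intervention 01/11/2008 – 31/07/2011", then six excluded months, then 12 months.
- Shared year: "Post-intervention period for TXA policy is the same as the pre-intervention period for anaemia screening programme analysis".
- Anaemia screening: "this period will be cut to include only 12 time points, after the 6 month lag period, for the primary analysis".
- Both gaps: "Lag periods will be accounted for by excluding this data from the primary analysis".

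The article also plans a sensitivity analysis with a lag of 12 time points for seasonality, and says the effect of its autocorrelation adjustments will be tested in sensitivity analyses. It names no alternative method for that test.

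**The concern.** Positive autocorrelation makes the ordinary standard errors of a segmented regression too small. A valid remedy has to enlarge them. Adding the lagged residual as a regressor whitens the residuals but does not restore the missing variance of the level and slope estimates. The diagnostics would look better while the test stays as it was.

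Both primary ITS analyses (TXA policy, and anaemia screening in all patients) rely on this step for the stated 0.05 level and 95% intervals. If it fails when needed, a level change in transfusion could be declared too readily and reported with too narrow an interval.

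**Working it through.** The plan gives no power or error-rate figure for the ITS, so the benchmark is its own 0.05 level (two-sided assumed).

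**Inputs from the plan**
- TXA series: November 2008 to July 2011 is 2 + 12 + 12 + 7 = 33 months, then a 6-month gap, then 12 months (33/6/12).
- Anaemia primary series: 12/6/12.
- Anaemia long sensitivity series: August 2013 to February 2019 is 5 + 60 + 2 = 67 months (12/6/67).
- About 100 procedures a month (Addressing threats to validity).

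**Assumed, not in the plan:** AR(1) errors with lag-1 correlation rho.

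**Algebra.** Let X hold intercept, time, level change and slope change, and let e be the residuals of the first fit. Then X'e = 0, and the lagged residuals are nearly orthogonal to X. Adding them leaves the coefficients close to least squares. Their standard errors are still read from s²(X'X)⁻¹, with s² now the smaller innovation variance. The true variance, (X'X)⁻¹X'ΩX(X'X)⁻¹, is larger when rho > 0.

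For slowly varying regressors in a long series, the ratio of reported SE to true SD is about √((1 − rho)/(1 + rho)) for least squares and about 1 − rho with the lagged residual. The false-positive rate is then about 2Φ(−1.96 × ratio):
- rho 0.2: ratios 0.816 and 0.80, rates 11.0% and 11.7%.
- rho 0.4: ratios 0.655 and 0.60, rates 19.9% and 24.0%.

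So length does not cure the problem.

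**Simulation for the planned series.** No intervention effect, Gaussian AR(1) errors, 4,000 runs per setting (1,500 for REML). False-positive rate for the level change:

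| Series | rho | Least squares | Lagged residual | REML AR(1), calendar time |
|---|---|---|---|---|
| 12/6/12 | 0 | 5.1% | 5.0% | 6.3% |
| 12/6/12 | 0.2 | 10.1% | 9.8% | 7.5% |
| 12/6/12 | 0.4 | 18.7% | 17.8% | 9.6% |
| 33/6/12 | 0 | 5.4% | 5.3% | 6.0% |
| 33/6/12 | 0.2 | 11.1% | 11.0% | 6.5% |
| 33/6/12 | 0.4 | 19.3% | 20.1% | 6.7% |

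Monte Carlo standard error is √(0.18 × 0.82/4000) = 0.6 points near 18%. Repeat runs put the lagged-residual rate at 9.3 to 11.0% for rho 0.2 and 16.3 to 20.1% for rho 0.4. With the lagged residual, mean SE over true SD is 0.83 and 0.65 (12/6/12), and 0.81 and 0.65 (33/6/12), at rho 0.2 and 0.4. The slope change behaves alike: 16.9% and 17.6% at rho 0.4. In 12/6/67 at rho 0.4 the lagged residual raises the level-change rate from 15.2% to 16.9%. At rho −0.2 the tests are conservative (about 3%).

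**The gap.** The first post-intervention month has no lag-1 residual: the preceding data row is seven months earlier. The plan does not say how this is handled. Dropping the first point of each segment gives 18.4% and 19.9% at rho 0.4, so the conclusion does not depend on it.

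**Binomial noise.** For proportions from n = 100, with base rate p and latent AR(1) drift of SD s, observed rho = latent rho × s²/(s² + p(1 − p)/n). Take p = 5% or 10% and latent rho 0.4 or 0.6, all assumed.
- s = 1 percentage point: lowest 0.4 × 0.0001/(0.0001 + 0.0009) = 0.04; highest 0.6 × 0.0001/(0.0001 + 0.000475) = 0.10. Lagged residual: 6.3 to 8.5% (12/6/12) and 6.2 to 8.6% (33/6/12). REML: 6.5 to 8.3% and 5.3 to 7.3%.
- s = 2 points: observed rho 0.12 to 0.27. Lagged residual: 9.4 to 14.9% and 8.6 to 17.6%. REML: 8.3 to 11.5% and 7.2 to 12.3%.

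A further set under moderate drift gave 6 to 12% for the lagged residual, with REML at 7.6 to 11.0% (12/6/12) and 6.2 to 9.0% (33/6/12). With larger drift on the logit scale (latent rho 0.6, SD 0.2 to 0.4, rates 5 to 20%), the lagged residual gave 8.8 to 22.3% and 9.4 to 24.7%.

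**The case against.** **The sentence may mean something else.** An error term that depends on its own lag could loosely be described in these words, and the cited sources are not at hand. If a jointly estimated AR(1) error model is meant, most of the criticism falls away. This stands as a condition on the finding, but the wording has residuals entering the model, so it needs correcting either way.

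**The harm is conditional.** A reader might infer that the ITS p-values will be too optimistic. The plan does not support that: it reports no autocorrelation, there is no harm at rho 0, and the tests are conservative at negative rho. What remains is that the adjustment exists only for autocorrelation and does nothing useful when autocorrelation is positive.

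**The upper figures overstate the risk for the primary outcome.** This largely stands. An observed rho of 0.4 was not reached in the percentage-point drift settings above. Under small drift, REML gains little or nothing over the lagged residual with 24 points.

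**The plan already covers it.** Comparing ITS and RDD acknowledges autocorrelation, and sensitivity analyses are promised. But no valid alternative is named, and the primary p-values would not change.

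**Scope.** A reader might extend the point to every ITS analysis. The secondary anaemia analyses use a non-anaemic control cohort, in which shared serial variation may partly cancel. They were not simulated, so nothing is claimed for them.

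**Conclusion.** The point holds, conditionally, for the two primary uncontrolled segmented regressions. On the plain reading, the stated adjustment leaves the level and slope tests at the uncorrected least-squares error rate: about 10% at observed rho 0.2, 16 to 20% at 0.4, and about 5% at 0. For monthly proportions from about 100 procedures, roughly 6 to 12% is the more realistic range under moderate drift, and more if drift is large. All rho and drift values are assumptions.

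It would also be wrong to infer that an AR(1) model solves everything. It brings the TXA series to about 6.5 to 7% in the Gaussian runs at rho 0.2 to 0.4, but leaves the 24-point anaemia series at about 7.5 to 9.6%. Autocorrelated drift plus binomial noise is not itself exactly AR(1). The change is worth making because the present step does not serve its only purpose and the replacement is cheap.

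**What to change.** Replace the sentence on lagged residuals with wording such as:

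> The two primary segmented regressions will be fitted by generalised least squares with AR(1) errors, estimated by REML on calendar month, so that the six excluded months count as elapsed time. Tests and intervals will use a t reference with small-sample degrees of freedom. A model with the lag-1 residual as a covariate will be reported as a sensitivity analysis.

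Name the degrees-of-freedom method, and state that p-values and intervals from the 12/6/12 series are approximate. If an AR(1) error model was intended all along, say so and state how the gap is treated.

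**Cost:** SAP wording and a few lines of R; Study status says analysis is still pending. The downside is that with 24 points and no autocorrelation, REML rejected 6.3% in one set of runs and 7.7% in another, against 5.0% and 5.8% for the lagged residual. The error rate under a specific small-sample degrees-of-freedom method was not simulated, so full restoration of 5% should not be promised.
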